### Sample size

Sample size and power calculations for the primary analysis are centered on the expected weight loss at the 6-month endpoint. Based on the findings from Winslow et al., which indicated a significant weight reduction of 6.5 kg (95% CI: −10.0, −3.0) between treatment groups following 6 months of phentermine/topiramate therapy, we have designed our study to detect a similar effect [4]. To ensure adequate statistical power, we plan to recruit a total of 58 participants, with 29 assigned to each treatment arm. This sample size accounts for a projected attrition rate of 30% at 6 months, as observed in Poulton et al. [5]

The sample size calculation was based on 6-month outcomes, and that analyses at 2 years should be interpreted as exploratory and hypothesis-generating.

### Baseline investigations

a)Electrocardiography (ECG)b)Echocardiogram (ECHO)c)Blood biochemistry: Full Blood Count (FBC), Liver Function Tests (LFT), Electrolytes, Urea, and Creatinine (EUC), glucose, insulin, HbA1c, lipids, Thyroid-Stimulating Hormone (TSH), and high-sensitivity C-reactive protein (Hs-CRP)

### Baseline measures

At baseline, a comprehensive assessment will be conducted to gather key demographic information, including age, gender, and socio-economic status, as well as clinical data related to comorbidities such as hypertension, diabetes, cardiovascular disease, and sleep disorders. Additionally, psychosocial factors will be evaluated, including lifestyle behaviours, dietary patterns, physical activity levels, and mental health status, such as stress, depression, or anxiety, all of which could impact weight management outcomes. Anthropometric measurements will be recorded, including weight, height, BMI, and waist circumference.

Participants will also have an initial consultation with a dietician, during which personalised dietary recommendations and exercise plans will be provided, aligning with the overall goal of facilitating long-term weight loss. This consultation will serve as the foundation for the ongoing diet and exercise program throughout the trial.

Table 1 outlines the full range of data to be collected and their frequency of collection during the study. Regular monitoring of vital signs, assessment of adherence to diet and exercise programs, and weight will take place, alongside evaluations of psychotropic effects using standardised scales such as the Amphetamine Interview Rating Scale [6]. These parameters will be assessed at key intervals during the treatment phase. Adjustments will be made to study medication dosing and lifestyle intervention advice based on clinical grounds and questionnaire results to ensure patient safety and optimise outcomes.

**Table 1 tbl0001:** Schedule of Assessments and Data Collection. This table outlines the data collection schedule throughout the study, detailing the parameters recorded at baseline, during dose changes, maintenance, and after ceasing treatment.

	Baseline	Pre dose change	Maintenance	After ceasing
***Anthropometric data***				
*Weight*	X	X	X	X
*Height*	X			
*Waist circumference*	X			X
*Blood pressure*	X	X	X	X
*Heart rate*	X	X	X	X
***Demographic data***				
*Age*	X			
*Gender*	X			
*Enrolment questionnaire*	X			
*Other Medications*	X	X	X	X
***Investigations***				
*Echocardiogram*	X			X
*ECG*	X		X	
*Blood test (fasted)*	X			X
***Questionnaires***				
*PHQ-9 for depression*	X			X
*Amphetamine interview rating scale*	X	X	X	X
*Exercise and diet assessment form*	X	X	X	X

### Randomisation and blinding

Participants will be randomised to receive either immediate-release DEX tablets or a placebo, following a pre-determined randomisation sequence generated by a computer system. The allocation ratio will be 1:1, using a block size of 4. The DEX and placebo tablets will be identical in appearance and dispensed in containers that conceal the treatment allocation. Participants and investigators will remain blinded throughout the study. Unblinding will only occur if clinically necessary, such as in cases of severe adverse reactions or medical emergencies where knowledge of the treatment allocation is essential for patient safety. Blinding efficacy will be assessed at the end of the intervention using the Bang Blinding Index (BBI) for both participants and investigators to evaluate the success of treatment allocation concealment.

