### Recruitment

Participants will primarily be recruited through general practices, using flyers and direct GP referrals. Additional recruitment methods may include digital and social media advertisements, as well as articles in community newspapers.

Potential participants will first undergo a screening interview to assess their eligibility, followed by baseline investigations for those deemed likely to qualify. Once eligibility is confirmed, informed consent will be obtained, and participants will be randomised (see Fig. 1).

GPs with an interest in obesity management, and who are able to commit to the study requirements, will be recruited as study investigators. These GPs will be trained in the study protocol and procedures, with training provided by a member of the research team.

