### Dose titration

Treatment will commence with either DEX or placebo tablets at a dose of 5 mg (1 tablet) twice daily. Participants will then undergo weekly incremental increases of 5 mg (1 tablet) twice daily as tolerated, up to a maximum dose limit of 30 mg (6 tablets) twice daily. Dosage adjustments will be primarily guided by any adverse effects experienced, which will be evaluated through patient history, the AIRS, and measurements of blood pressure (BP) and heart rate.

Down titration of the study medication dose will occur if a participant reports significant adverse effects such as increased anxiety, adverse mood changes, or severe insomnia. Additionally, if BP readings exceed 140/90 mmHg or heart rate increases beyond 100 beats per minute, this may also prompt a dose adjustment. Conversely, if participants demonstrate good tolerance with minimal side effects, stable BP readings within normal limits, and a heart rate under 100 beats per minute, the current dose may be maintained. In the final month of treatment, the dosage will be gradually reduced by 10 mg (2 tablets) each week to ensure a gradual tapering process.

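### A single published block size of 4 makes up to a third of allocations deducible in the worst case; varied, undisclosed sizes remove most of that certainty but little of the guessing

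*Protocol article*

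**What the plan says.** Under Randomisation and blinding, participants are allocated "following a pre-determined randomisation sequence generated by a computer system", and the article adds "The allocation ratio will be 1:1, using a block size of 4". It mentions neither varying block sizes nor withholding the size from investigators. The safeguards it lists are "The DEX and placebo tablets will be identical in appearance and dispensed in containers that conceal the treatment allocation" and "Participants and investigators will remain blinded throughout the study", with unblinding allowed when clinically necessary. Blinding is to be checked with the Bang index once the intervention ends.

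Under Recruitment, "GPs with an interest in obesity management, and who are able to commit to the study requirements, will be recruited as study investigators", and "These GPs will be trained in the study protocol and procedures". Participants come mainly through general practices and GP referral. The Design overview has a clinician see each participant weekly for the six weeks of titration, then monthly. Under Dose titration, adverse effects are "evaluated through patient history, the AIRS, and measurements of blood pressure (BP) and heart rate", and Table 1 adds weight before each dose change.

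The article does not say how many GPs or practices take part, or whether there is one central list or one per practice.

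**The concern.** Identical tablets and concealing containers hide what is in the bottle. They do not hide what a stimulant may do to appetite, mood, sleep, heart rate, blood pressure and weight, and these are the things reviewed each week. A clinician who forms a view of past allocations and knows that every four participants split two and two can work out some later ones. An emergency unblinding reveals one member of a block outright.

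Foreknowledge opens the way to selective enrolment. In a trial of 58, a few steered enrolments could shift baseline weight or motivation between arms. The planned covariates include baseline BMI but not motivation. The Bang index is taken at the end and measures blinding, so it can neither prevent nor detect prediction of the next allocation.

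**Working it through.** The inputs are a block size of 4 at 1:1 (Randomisation and blinding) and a list of 58 (Sample size). The plan gives no predictability figure to reproduce. The accuracy with which clinicians infer past allocations, and the number of GPs sharing a list, are assumptions and are shown as ranges.

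**Certain allocations, perfect inference.** In a block of 4 the fourth allocation is always determined. The third is determined when the first two agree, with probability 1/3.
- Per block: (1 + 1/3)/4 = 1/3.
- Over 58 (14 full blocks and 2 left over): 14 × (4/3)/58 = 32%.

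**Correct best guesses, perfect inference.** By position these are 1/2, 2/3, 2/3 and 1.
- Per block: (1/2 + 2/3 + 2/3 + 1)/4 = 17/24 = 71%.
- Over 58: (14 × 17/6 + 7/6)/58 = 70%, against 50% by chance.

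**Imperfect inference and varied blocks.** Lists of 58 were simulated with an optimal guesser who knows which sizes are in use. Each cell gives the share certain, then the share guessed correctly.

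| Accuracy of inferring past arms | Fixed 4 | Random 4/6 | Random 4/6/8 |
|---|---|---|---|
| 100% | 32%, 70% | 5%, 69% | 2%, 68% |
| 90% | 0%, 65% | 0%, 61% | 0%, 60% |
| 80% | 0%, 60% | 0%, 58% | 0%, 57% |
| 70% | 0%, 56% | 0%, 55% | 0%, 54% |

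A guesser who ignores block sizes and always picks the arm that is behind scores the same under perfect inference: 70%, 69% and 68%.

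**Delay.** If the most recent participant's arm is not yet apparent, only the fourth allocation can be certain, and only when the first two agree: (1/3)/4 = 8%. If the two most recent are not apparent, the share is 0%.

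**Shared list.** Suppose k GPs recruit equally from one list, each sees only their own patients, and block boundaries are known. The two earlier allocations that settle the matter must both be the GP's own, with probability 1/k². The certain share is then (1/3)/k²: 8% for k = 2, 4% for k = 3 and 1% for k = 5. Simulation agrees.

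**Blocks of 2.** Under perfect inference, random 2/4 gives 11% certain and 72% guessed, and 2/4/6 gives 4% and 70%. Neither lowers guessing below the fixed block of 4.

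**Balance.** At 58 the largest arm difference is 2 with fixed 4 (the last block is cut in half), 2 with 4/6 and 4 with 4/6/8.

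**The case against.** The strongest reply is that the worst case is far from what the article describes. It speaks of one pre-determined sequence and of GPs in the plural, and mentions no stratification by practice. Doses start low and rise over six weeks, so effects may take time to show. Under a shared list, delay or imperfect inference, certainty falls to 8% or less. Regression adjustment for baseline BMI, age, sex and comorbidities would absorb part of any imbalance. How the list is held is a detail that an article may leave to the full protocol or procedure manual. All of this stands and limits the size of the point. It does not remove it, because the article itself prints the block size.

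A reader might infer more than the text supports:
- *GPs will know upcoming allocations.* At most about a third could be known, and only with error-free, timely inference and sight of the whole list. The article does not show how well drug effects reveal the arm.
- *The same GPs refer, enrol and review.* The article mentions GP referral and GP investigators separately, has a clinician do the reviews, and lets other trained personnel collect data. Overlap is plausible but not stated.
- *Varied blocks largely prevent prediction.* This is true of certain knowledge only. Better-than-chance guessing remains, and that is enough for some selective enrolment.
- *The change costs nothing.* With 4/6/8 the possible final arm difference rises from 2 to 4.

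**Conclusion.** The point holds as a minor weakness in a stated design choice. The article contains no contradiction or wrong figure here. Publishing one block size of 4 leaves up to about 32% of the 58 allocations certain and about 70% guessable, both as upper bounds. With 90% accurate inference the figures are 0% and 65%. On a list shared by two or more GPs in equal numbers, each seeing only their own patients, the certain share per GP is about 8% or less.

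Varying the sizes is worthwhile mainly because it removes most of the certain knowledge. Its effect on guessing is 1 to 2 percentage points under perfect inference and about 4 at 90% accuracy. The conclusion assumes some functional unblinding by drug effects, which the documents make plausible but do not quantify. It also assumes that the block size in the article is the one in use and can be learned by investigators.

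**What to change.** Before recruitment starts, or for the remaining allocations if it has started, generate the list with permuted blocks of randomly varying size, for example 4 and 6, or 4, 6 and 8. Avoid blocks of 2. Let only the statistician or pharmacy that holds the list know the sizes, and keep them out of the protocol and the training material. Replace the statement of a single size with: *randomly varying block sizes not disclosed to investigators*. Because size 4 is already public, a reworded sentence is not enough; the list itself has to be regenerated. It would also help to state whether the list is central or per practice, since the exposure depends heavily on that.

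The cost is regenerating the list. With 4/6 the largest final arm difference stays at 2 participants; with 4/6/8 it rises to 4.

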### Dose titration

Treatment will commence with either DEX or placebo tablets at a dose of 5 mg (1 tablet) twice daily. Participants will then undergo weekly incremental increases of 5 mg (1 tablet) twice daily as tolerated, up to a maximum dose limit of 30 mg (6 tablets) twice daily. Dosage adjustments will be primarily guided by any adverse effects experienced, which will be evaluated through patient history, the AIRS, and measurements of blood pressure (BP) and heart rate.

Down titration of the study medication dose will occur if a participant reports significant adverse effects such as increased anxiety, adverse mood changes, or severe insomnia. Additionally, if BP readings exceed 140/90 mmHg or heart rate increases beyond 100 beats per minute, this may also prompt a dose adjustment. Conversely, if participants demonstrate good tolerance with minimal side effects, stable BP readings within normal limits, and a heart rate under 100 beats per minute, the current dose may be maintained. In the final month of treatment, the dosage will be gradually reduced by 10 mg (2 tablets) each week to ensure a gradual tapering process.

### Study questionnaires

The Patient Health Questionnaire for Depression (PHQ-9) is a widely utilised and validated tool that assesses the severity of depression in both clinical and research settings [7]. This questionnaire evaluates each of the nine criteria outlined in the Diagnostic and Statistical Manual of Mental Disorders, Fourth Edition (DSM-IV), using a rating scale that ranges from 0 (not at all) to 3 (nearly every day). Administered at baseline, the PHQ-9 serves as a critical screening instrument for identifying active depressive disorders.

Similarly, the Ampetamine Interview Rating Scale (AIRS) is a validated scale employed throughout the treatment period, particularly during dose titration, to monitor participant responses. This scale comprises 34 questions with graded responses based on a Likert scale, covering various symptom categories, including much less than normal, less than normal, normal, more than normal, and much more than normal. The AIRS evaluates important factors such as hunger, mood, and sleep, with self-rated responses guiding dose adjustments as needed [6].

Additionally, the exercise-diet assessment form has been developed by the research team as a practical tool for tracking daily physical activity and dietary indiscretions. Participants complete this form weekly, and it is reviewed in consultations with their clinician. Moreover, it serves as an adherence record for researchers, ensuring that both dietary and exercise commitments are monitored effectively throughout the study.

### Outcome measures

Outcome measures will be collected at baseline, during each dose adjustment visit, during the maintenance phase of treatment, and following cessation of medication at 1 week, and at 1, 3, 6, 12, 18, and 24 months, as illustrated in Fig. 1.

Primary Outcome• Change in Body Weight: Change in body weight from baseline measured at 6 months during treatment and at 2 years following discontinuation of study medication.

Secondary Outcomes1.Cardiovascular Outcomes: Changes in cardiovascular parameters and the incidence of adverse cardiovascular events.2.Baseline Mental Health Assessment: Identification of possible undiagnosed active depressive disorders at baseline.3.Neuropsychiatric Effects: Changes in mood, cognition, and physiological responses during treatment as measured by the Amphetamine Interview Rating Scale (AIRS).4.Feasibility will be assessed by recruitment and retention rates, treatment adherence, ability to achieve target dosing, and the frequency of adverse events or treatment discontinuation.

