### Study objectives

#### Primary objective

To evaluate the effect of DEX treatment on body weight in patients with obesity managed in general practice.

Secondary Objectives1.To assess the cardiovascular safety of DEX treatment through monitoring of cardiovascular parameters and the occurrence of adverse cardiovascular events.2.To identify possible undiagnosed active depressive disorders at baseline prior to initiation of treatment.3.To evaluate changes in mood, cognition, and physiological responses during treatment using the Amphetamine Interview Rating Scale (AIRS).4.To assess the feasibility of implementing DEX therapy for obesity management within routine general practice care, as measured by recruitment, retention, adherence, and tolerability.

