### Participants

Potential participants will be screened to determine whether they meet inclusion criteria and any exclusion criteria prior to recruitment.

Inclusion Criteria:a)Adults aged 18–70 yearsb)BMI 25–70c)Medically stable, defined as no acute medical illness within the past 3 months, no uncontrolled chronic disease, and no recent changes in medications within past 3 months.

Exclusion Criteria:a)Significant cardiac valve disease, cardiomyopathy, or arrhythmiab)Symptomatic ischemic heart diseasec)History of addiction to illicit drugsd)Uncontrolled hypertension >140/90e)Significant kidney or liver diseasef)Uncontrolled epilepsyg)Breastfeeding, pregnant, or planning pregnancyh)Current depression or other psychiatric illnessi)Current or recent treatment (past 12 months) with psychotropic medication, systemic glucocorticoids, or weight loss medication (e.g., orlistat, phentermine)j)Family history of sudden death from cardiac causesk)Hypersensitivity to DEX or any components of the DEX or placebo tablet

All participants will be fully informed about the purpose of the study, the therapeutic and adverse effects of DEX, and will provide informed consent. Each participant will be assigned a unique study number, and data will be collected and analysed in a de-identified but re-identifiable form.

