### Data analysis

The primary analysis will adopt an intention-to-treat approach to ensure that all randomised participants are included in the evaluation, regardless of adherence to the treatment protocol. The primary outcome, the change in weight from baseline to both 6 months and 2 years, will be assessed using simple and multiple linear regression, adjusting for prespecified covariates such as age, sex, baseline BMI, and comorbidities. Secondary outcomes, including cardiovascular parameters, mood and cognition (AIRS scores), and feasibility metrics, will be analysed using appropriate regression models or repeated-measures mixed-effects models for longitudinal data. Missing data will be addressed primarily using available data under intention to treat; where missingness exceeds 10–15%, multiple imputation and complete-case analyses will be conducted as sensitivity analyses. Exploratory subgroup analyses by sex, baseline BMI, or baseline depressive status may also be performed. Adverse events will be summarised descriptively by type, severity, and relationship to treatment, with serious events reported individually.

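### Secondary outcome 2 is a pre-treatment screening result that conflicts with exclusion (h); as written, baseline investigations precede consent, and the PHQ-9 taken after treatment has no stated use

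*Protocol article*

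**What the plan says.** All places are in the protocol article.

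- **Study objectives**, secondary objective 2: "To identify possible undiagnosed active depressive disorders at baseline prior to initiation of treatment".
- **Outcome measures**, secondary outcome 2: "Identification of possible undiagnosed active depressive disorders at baseline". It has no change component and no comparison between arms.
- **Participants**: exclusion criterion (h) bars people who currently have depression or another psychiatric illness. On timing: "Potential participants will be screened to determine whether they meet inclusion criteria and any exclusion criteria prior to recruitment".
- **Study questionnaires**: "Administered at baseline, the PHQ-9 serves as a critical screening instrument for identifying active depressive disorders".
- **Recruitment**: a screening interview comes first, then baseline investigations for those likely to qualify, and then "Once eligibility is confirmed, informed consent will be obtained, and participants will be randomised". The section Baseline investigations lists these as ECG, echocardiogram and blood biochemistry.
- **Table 1**, questionnaire block: the row "PHQ-9 for depression" is marked at baseline and again after ceasing treatment.
- **Data analysis**: the outcomes named for secondary analysis are "Secondary outcomes, including cardiovascular parameters, mood and cognition (AIRS scores), and feasibility metrics". On subgroups: "Exploratory subgroup analyses by sex, baseline BMI, or baseline depressive status may also be performed".

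**The concern.** Three connected things do not fit together.

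1. The trial excludes people with current depression, uses the PHQ-9 at baseline to look for it, and then lists the finding as a secondary outcome and as a possible subgroup factor. The exclusion removes the people whom the outcome and the subgroup need.
2. The stated order puts research investigations before informed consent. Anyone who drops out of screening at that stage has had study tests without having consented.
3. The PHQ-9 is collected again after treatment stops, which would allow a randomised comparison of depressive symptoms after withdrawal of a stimulant. No stated objective, outcome or analysis makes that comparison.

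At stake are a secondary objective that tells the reader nothing about the treatment, a subgroup that may have almost nobody in one level, participant protection at screening, and a safety question that the collected data could address.

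**Working it through.** The documents give no figure for depression, so there is none to reproduce. The check is mainly a comparison of sections.

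**Step 1: outcome against exclusion.**

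| If a PHQ-9 positive is… | Secondary outcome 2 among randomised participants | Depressed/not-depressed subgroup | Exclusion (h) |
|---|---|---|---|
| treated as current depression and excluded | few or no cases | one level nearly or wholly empty | applied |
| randomised | some cases | two levels, one small | not applied to cases the screen detects |

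On both rows the result is fixed before treatment starts, so it cannot differ between arms because of treatment.

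**Step 2: how many people could be in the depressed level?** Sample size gives 58 participants, 29 per arm, and 30% attrition at 6 months. The share p who are depressed despite the exclusion is not in the documents and is assumed here. Expected number = 58 × p; chance that a given arm has none = (1 − p)^29.

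| Assumed p | Expected of 58 | Per arm | Left after 30% attrition (× 0.7) | Chance that a given arm has none |
|---|---|---|---|---|
| 2% | 1.2 | 0.6 | 0.8 | 56% |
| 5% | 2.9 | 1.5 | 2.0 | 23% |
| 10% | 5.8 | 2.9 | 4.1 | 5% |

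**Step 3: what could that level show about weight?** Take SD = 8.4 kg, reading the ± in Protocol validation (10.6 ± 8.4 kg) as a standard deviation. With m people per arm in the stratum, the 95% half-width is 1.96 × 8.4 × √(2/m).

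- 3 people (m = 1.5): 1.96 × 8.4 × √(2/1.5) = 19.0 kg; power for 6.5 kg about 10%.
- 6 people (m = 3): 1.96 × 8.4 × √(2/3) = 13.4 kg; power for 6.5 kg about 16%.

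Both half-widths are more than twice the 6.5 kg the trial is designed to detect. They use the normal approximation, which is optimistic at these sizes.

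**Step 4: consent order.** Recruitment gives interview, baseline investigations, confirmed eligibility, consent, randomisation. The Specifications table says that consent precedes inclusion in the study. That does not alter the order, because inclusion comes after the investigations. The PHQ-9 is not in the list under Baseline investigations, so its place relative to consent is not stated.

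**Step 5: use of the second PHQ-9.** Secondary objectives 1 to 4, secondary outcomes 1 to 4 and Data analysis contain no use of a post-treatment PHQ-9. The depression outcome is tied to baseline. The mood outcome is the AIRS, which Outcome measures ties to the treatment period and Data collection ties to the time on study medication.

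**Step 6: what a between-arm PHQ-9 comparison could deliver.** After 30% attrition, 29 × 0.7 = 20.3, so about 20 per arm. Unadjusted 95% half-width in SD units = 1.96 × √(2/20) = 0.62. Adjustment for baseline would narrow this; further loss after 6 months would widen it. It is an estimate with an interval, not a powered test.

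**The case against.** The strongest reply is that the documents never say that a positive PHQ-9 triggers exclusion (h), and they give no cut-off. Secondary outcome 2 concerns possible undiagnosed disorders, which is a flag and not a diagnosis, and the objective places it before treatment, not before randomisation. Known depression could be excluded at interview and the PHQ-9 then used to pick up missed cases. Nothing restricts the outcome to randomised participants, so it can be read as screening yield. This stands against stronger readings that a reader might infer: that exactly 0 of 58 will be depressed, that the subgroup must be empty, or that the screening result cannot be reported. None of these is in the text. It does not remove the conflict with exclusion (h) for flagged people who are randomised, and screening yield is still not an effect of treatment.

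The subgroup is optional and exploratory, and depressive status is undefined. It could rest on score level, which would avoid an empty category. This also stands, and it is why redefinition is offered as an alternative to deletion.

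A reader might also infer that PHQ-9 data are taken before consent. The text does not say so, and the flow figure to which Recruitment refers is not shown. For ECG, echocardiogram and bloods, the written order is explicit.

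Finally, depressive symptoms after stopping are not wholly unobserved. Table 1 also marks the AIRS after ceasing, and adverse events are recorded throughout. The list in Data analysis is introduced as non-exhaustive, and an analysis plan not shown might use the later PHQ-9. So the claim is limited to this: no objective, outcome or analysis stated in the article uses it.

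**Conclusion.** The point holds in this form. Secondary outcome 2 is a screening result that randomised treatment cannot affect, and its relation to exclusion (h) is unresolved: either few or no cases remain, or the exclusion is not applied to cases the trial detects. The exact number is unknown. Under assumed shares of 2% to 10% it is about 1 to 6 of 58, too few for a depressed/not-depressed comparison of weight loss.

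As written, ECG, echocardiogram and bloods precede informed consent. This is the most serious part for participants. The post-cessation PHQ-9 is collected without a stated use, while the AIRS outcome is limited to treatment.

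The primary weight outcome is not affected, and the subgroup is only exploratory. The change is worth making because it is cheap and improves both participant protection and the safety information.

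**What to change.** 1. In Recruitment, place informed consent before the study-specific baseline investigations and the PHQ-9, and state where the PHQ-9 falls.
2. Reconcile the PHQ-9 screen with exclusion (h): say how a positive result bears on eligibility. Report screen-positives descriptively among all consented, screened people, and remove this item from the trial outcomes.
3. Drop the subgroup by baseline depressive status, or redefine it as an exploratory interaction of treatment with the continuous baseline PHQ-9 score.
4. Add as a secondary safety outcome the between-arm difference in post-cessation PHQ-9, adjusted for baseline PHQ-9. Name the visit, because Table 1 has one column for all visits after ceasing. Report the estimate with its 95% interval.

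**Cost:** amendment wording, consent from some people who then fail screening, and one additional secondary analysis. No new measurement is needed.
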